**Methods:**

RedeS is a Phase 3, prospective, multi-center, randomized, double-blind, active-controlled, parallel-design study, with a 6-month extension option to evaluate patients requiring repeated transfusions including red cell exchange (RCE). Eligible subjects will be stratified according to site, baseline bleeding status and participation in the extension period. The study arms include a transfusion period of 28-days for anemia with any bleeding or non-bleeding patients or a 28-day + 6-month extension for non-bleeding patients with chronic anemia requiring repeated simple transfusions, or for patients with sickle cell disease (SCD) expected to receive three RCE procedures.

The study will seek to enroll 600–800 subjects in the overall safety analysis, including ~ 140 repeatedly-transfused subjects in the 6-month extension including up to 30 subjects receiving three RCE procedures. The primary safety endpoints are the proportion of patients with any treatment-emergent adverse events (TEAEs) related to study RBC transfusion through 28 days after the last study transfusion, and the proportion of patients with treatment-emergent antibodies with confirmed specificity to PR-RBCs. The primary efficacy endpoint is the hemoglobin (Hb) increment in subjects who are non-bleeding at baseline, adjusted for the grams of Hb transfused and averaged over multiple transfusions. With 352 evaluable transfused non-bleeding subjects (176 per treatment group) from either arm, the study will have 80% power to demonstrate non-inferiority, defined as a Hb increment treatment difference of no more than 15% of the Control group mean, assuming a Control arm coefficient of variation of 50%.

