### Randomization

An Interactive Web Response System (IWRS) will be used for electronic randomization of eligible patients. At the end of screening and prior to the first study RBC transfusion, the patient’s eligibility status will be entered into the study EDC system. If eligible, the patient will be randomized to receive either amustaline/GSH or conventional RBCs in a 1:1 ratio. Randomization will be stratified by site, baseline bleeding status (indication for RBC transfusion due to active bleeding or for anemia without active bleeding), patients’ participation in the optional extension period, and patients’ need for RCE (Fig. 2). Active bleeding will be defined as Grade 3 or 4 bleeding of the expanded WHO bleeding scale. Anticipated surgical bleeding and planned blood loss/replacement through RCE at baseline should be included as active bleeding (Grade ≥ 3) by definition.

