## Outcomes

### Primary and secondary endpoints

The primary safety endpoints include the proportion of subjects with any TEAEs possibly, probably or definitely related to a study RBC through 28-days after the last study transfusion, and the proportion of subjects with treatment-emergent antibodies with confirmed specificity to PR-RBCs. The primary efficacy endpoint is the adjusted Hb increment averaged over multiple transfusions for all non-bleeding subjects at baseline, defined as the difference between pre- and 15-min-24 h post-transfusion Hb values divided by the total Hb content transfused during each transfusion episode.

Secondary efficacy and safety endpoints will include:Adjusted Hb consumption defined as total Hb mass transfused (g) divided by body weight (kg) and the duration of the study transfusion period (days) in patients without active bleeding at baseline.HbA clearance in SCD patients undergoing regular RCE.All TEAEs for 28 days after last study transfusion.Transfusion reactions related to study RBCs (as defined by the CDC National Healthcare Safety Network [NHSN] Hemovigilance Module protocol), for 28 days after the last study transfusion.Treatment-emergent immunization to RBC alloantigens.All-cause mortality through 28 days after the last study transfusion.

Secondary Safety Endpoints (for SCD patients undergoing RCE):Proportion of subjects with adverse events of special interest (AESI) through 28 days after the last study transfusion.S-300 and GSH plasma levels before and 15 min to 4 h after RCE.

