Non-study RBCs received during the study transfusion period will be included in the calculation of Hb content transfused. For each non-study RBC component received, the Hb content will be imputed using the average Hb content per study RBC component from the Control group within each clinical site.

The treatment difference in the adjusted Hb increment will also be summarized descriptively (with a 95% confidence interval) as exploratory analyses for the following mITT subgroups:Repeatedly transfused non-bleeding patients (defined as non-bleeding patients who receive at least 3 study RBC episodes).Subgroup by clinical site, age group (< 18, 18–64, and ≥ 65 years old), sex, and race (e.g., white vs. other races), as appropriate.

For SCD patients enrolled in the 6-month extension for three RCE procedures, HbA clearance will be estimated from the area under the curve (AUC) calculated by the trapezoidal rule based on measurements from samples collected within 4-h of each RCE, on Day 14 (± 7-days) and prior to the next scheduled RCE. Values will be adjusted by the duration in days used to calculate the AUC (i.e., between the 15 min-to-4-h post-transfusion sample and pre-transfusion sample of the next transfusion) and averaged over all study RCE procedures for each patient.

For the secondary efficacy endpoint of Hb consumption, the analysis will be conducted only in non-bleeding mITT patients who participate in both of the initial 28-day and 6-month extension periods and will utilize integrated data from both periods. Treatment differences in non-bleeding mITT patients will be assessed using the same non-inferiority test methods described above for the primary endpoint analysis. Interaction terms between the treatment and covariates will be explored, as necessary. For the adjusted Hb consumption analysis, the upper bound of a two-sided 95% confidence interval for the treatment difference (Test – 1.15 × Control) less than or equal to zero will result in the rejection of inferiority null hypothesis and the conclusion of non-inferiority.

Adjusted Hb consumption will be calculated as total Hb mass transfused in grams divided by body weight in kg at baseline and duration of the study transfusion period in days (g/kg/day). The total Hb mass transfused is the sum of the Hb content for all study and non-study RBC components transfused during the study transfusion period (i.e., 28 days or 28-day + 6-months, unless subjects prematurely discontinue the study).

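### The population for the Hb-consumption non-inferiority test is not reconciled, and read literally the narrower version selects subjects after randomization

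*Protocol article*

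**What the plan says.** Four parts of the protocol article bear on who enters this analysis.

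- **Primary and secondary endpoints** defines adjusted Hb consumption as Hb mass divided by body weight and by "the duration of the study transfusion period (days) in patients without active bleeding at baseline". The extension is not mentioned.
- **Statistical methods**, in the paragraph on this endpoint, says that "the analysis will be conducted only in non-bleeding mITT patients who participate in both of the initial 28-day and 6-month extension periods", using integrated data. The next sentence reads "Treatment differences in non-bleeding mITT patients will be assessed using the same non-inferiority test methods described above for the primary endpoint analysis" and does not repeat the limit. The decision rule is that the upper 95% bound of Test - 1.15 x Control is at or below zero.
- **Statistical methods**, in the calculation rules for the same endpoint, sums Hb mass over the study transfusion period, glossed as "i.e., 28 days or 28-day + 6-months, unless subjects prematurely discontinue the study". The rules for early discontinuation repeat the two planned lengths and give end dates for deaths and for other withdrawals.
- **Randomization** lists "patients’ participation in the optional extension period" as a stratification factor. Screening/randomization says that consent for the extension is obtained at initial enrollment.

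**The concern.** This endpoint has a formal pass/fail rule, so the analysis set should follow from the text without interpretation. Two things stand in the way.

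First, the endpoint definition and the analysis paragraph describe different sets, and the duration wording fits the wider one. Early discontinuation is dealt with separately, so the 28-day option reads as a planned length, and no extension subject has a 28-day plan. The readings differ in N and also in the question asked: consumption in acute and chronic recipients together, or in chronic recipients only.

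Second, the narrower set is itself loosely defined. Participating in both periods may mean being randomized in the extension stratum, or actually entering the second period. The latter is known only after randomization. It would drop extension-stratum subjects who die or withdraw in the first 28 days, although the article gives duration rules for deaths and withdrawals. Subjects who develop treatment-emergent antibodies to the pathogen-reduced cells are also taken off study transfusion, so losses before the extension need not be equal in the two arms.

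**Working it through.** **1. The plan's own figure.** The article gives a sample size only for the primary efficacy endpoint: margin 15% of the Control mean, CV 50%, no true difference, two-sided 0.05. In units of the Control mean:

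n per arm = 2 x (1.96 + z)^2 x 0.5^2 / 0.15^2

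- 80% power (z = 0.8416): 2 x 7.849 x 0.25 / 0.0225 = 174.4, so 175 per arm and 350 in total. The abstract has "With 352 evaluable transfused non-bleeding subjects (176 per treatment group) from either arm".
- 90% power (z = 1.2816): 2 x 10.507 x 0.25 / 0.0225 = 233.5, so 234 per arm and 468 in total, as stated.

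The primary-endpoint figures reproduce. (Sample size gives about 174 per group beside the same total of 352, whereas 352 / 2 = 176; 176 is used here.)

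**2. N on each reading.**

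- Wider: at least 352 non-bleeding evaluable subjects, 176 per arm.
- Narrower: the extension target is 140, including up to 30 red cell exchange subjects, whom Randomization classes as bleeding. That leaves 140 - 30 = 110 non-bleeding subjects, or up to 140 if no exchange subjects were enrolled: 55 to 70 per arm at 1:1.
- Ratio: 352 / 140 = 2.5 to 352 / 110 = 3.2.

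**3. Power for the stated contrast.** With no true difference and the same CV in both arms, Test - 1.15 x Control has, relative to the Control mean,

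SE = CV x sqrt((1 + 1.15^2) / n) = CV x sqrt(2.3225 / n), and power = Phi(0.15 / SE - 1.96).

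No CV is given for consumption, so 30% to 50% is an assumption; the 50% is borrowed from the Hb increment. Example, n = 55 and CV 50%: SE = 0.5 x 0.2055 = 0.1027; 0.15 / 0.1027 = 1.46; Phi(-0.50) = 0.31.

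| CV | 55 per arm | 70 per arm | 176 per arm |
|---|---|---|---|
| 30% | 68% | 78% | 99% |
| 40% | 45% | 54% | 90% |
| 50% | 31% | 38% | 74% |

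**4. CV at which each set reaches 80% power.** CV = 0.15 / (2.8016 x sqrt(2.3225 / n)) gives about 26% at 55 per arm, 29% at 70 and 47% at 176.

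**5. Post-randomization selection.** The documents give no count of extension-stratum subjects lost before Day 28, so this part cannot be sized. It rests on the wording alone.

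**The case against.** The strongest defence is that there is no contradiction. The analysis paragraph is the specific statement and uses the word only, so it can be read as narrowing a general endpoint list. That list says all non-bleeding subjects for the primary endpoint but does not say all for consumption. The following sentence need not repeat the limit. The 28-day wording may serve other purposes: Statistical methods promises summaries of the two periods together and separately, and it lists exploratory consumption subgroups. Participation is used under Randomization for a status fixed at entry, and the duration rules for deaths and withdrawals suggest that such subjects are kept.

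Much of this stands. A reader might infer that the plan contains two incompatible tests; the text does not go that far, because a narrowing reading is available. A reader might also infer that power differs more than two-fold. That is supported for N but not for power in general: with this contrast the power ratio exceeds 2 only when the CV is above about 40% at 55 per arm, or about 52% at 70 per arm, and the documents give no CV for consumption. Nor is any stated figure wrong, since no N or power is claimed for this endpoint. That the conclusion would reverse between readings is possible but not shown.

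The defence does not remove the problem. Nothing in the article ties the 28-day wording to the separate or exploratory summaries, and nothing says that participating in both periods means the randomized stratum. Each benign reading has to be supplied by the reader. The SAP, not seen here, may settle it; the article as written does not.

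**Conclusion.** The point holds as a failure to reconcile the analysis population of a formally tested secondary endpoint. Depending on the text followed, planned N is at least 352 or about 110 to 140. Power under an assumed CV of 30% to 50% is about 99% to 74% at 176 per arm, against 68% to 31% at 55 per arm. These powers assume no true difference, equal CV in both arms and the same CV in both populations; the last is unverified, since one set mixes acute and chronic recipients. The N figures are planning targets, not actual enrollment.

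The selection issue is the more substantive part. Read literally, the narrower set is conditioned on a post-randomization event, and a definition based on the existing stratum avoids this. Its numerical effect is unknown and may be small. The primary efficacy endpoint is unaffected.

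**What to change.** Before unblinding, name one population for the Hb-consumption test and use it in both Primary and secondary endpoints and Statistical methods.

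- **If the extension cohort is intended:** define it as non-bleeding mITT subjects randomized in the extension stratum, whether or not they reach the second period. Include early deaths and withdrawals using the duration rules already in Statistical methods. Align the endpoint list. Keep the 28-day duration wording only for separate-period or exploratory summaries, and say so. It would also help to acknowledge that about 55 to 70 per arm reaches 80% power only if the CV is about 26% to 29% or less.
- **If all non-bleeding subjects are intended:** delete the restriction to those in both periods.

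The cost is wording in the protocol and SAP. No new data are needed, because the extension stratum is recorded at randomization. The Discussion says that the study remains blinded, and the Participants section expects the last assessments in the third quarter of 2026, so on the article's account the change can still be made without knowledge of the results.

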## Methods/design

CLI 00126 (RedeS) is a randomized, double-blind, actively controlled, parallel group study with 1:1 allocation investigating the INTERCEPT Blood System for red blood cells in regions at potential risk for Zika virus transfusion-transmitted infections. It evaluates the safety and efficacy of amustaline/GSH RBCs compared to conventional RBCs in patients who require acute and long-term RBC transfusion support (clinicaltrials.gov: NCT03037164). The primary safety endpoint is the incidence of related treatment-emergent adverse events (TEAEs) that occur within 28 days of the last study transfusion. Additionally, because treatment-emergent and natural antibodies specific for amustaline/GSH RBCs have been described in patients exposed or never exposed to amustaline/GSH RBCs [9–11], the study is designed to evaluate the incidence, nature and clinical significance [12] of antibodies specific for amustaline/GSH PR-RBCs within 75 days of the last study transfusion.

The primary efficacy endpoint is the post-transfusion adjusted Hb increment assessed in all subjects who were non-bleeding at baseline (subjects with expected surgical bleeding or RCE are defined within the “bleeding” category).

RedeS is sponsored by Cerus Corporation (hereafter referred to as the Sponsor). The trial will be conducted according to the protocol subject to institutional review board (IRB) approval, the International Council on Harmonization E6 Good Clinical Practice (GCP), and applicable local/national regulatory requirements and laws. This report has been formatted using the SPIRIT reporting guidelines,(13) as described in the SPIRIT checklist provided in the supplemental materials. A summary of the study’s schedule of enrollment, interventions, and assessments is provided in Tables 1 and 2.

**Table 1 Tab1:** Schedule of enrollment, interventions, and assessments: 28-day acute transfusion support and 28-day + 6-month extension period assessments for patients receiving repeated simple transfusions Patient populations: 28-day: Bleeding and non-bleeding patients, all indications; 28-day + 6-Months: Non-bleeding Patients with Thalassemia, SCD, MDS, AA, Chemotherapy or other bone marrow failure syndromes

	**Enrollment & Allocation‡**	**Post-Allocation**			

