**Study Assessments**	**Screening**	**Transfusion Support Periods** • **Day 1 through Day 28 *****and*** • **28-Day plus 6-month extension (or death-up to 10 transfusion episodes)**		**Follow-Up Visit Day 28* (28 ± 7 days) after last study transfusion episode**	**End of Study-Day 75 of** ** Follow-Up (75 ± 15 days) after last study transfusion**
		**Before each transfusion episode**	**15 min—24 h. after each transfusion episode**		
Informed Consent (assent, if appropriate)	X^1^				
Medical, surgical, prior transfusion and medication history	X^1^				
Physical exam, including height	X^1^				
Weight	X^1^				
Demographics	X^1^				
ABO Blood type and Rh^3^	X^1^	X^3^			
Indirect Antiglobulin Test^3^	X^1^	X^3^		X	
DAT^8^	X^1^			X	X
Immune reactivity to amustaline/GSH RBCs (amustaline/GSH RBC antibody testing)	X^1^	X^7^		X	X
Pregnancy test (if applicable)^3^	X				
Indication for RBC transfusion	X^1^				
Hematology panel^9^	X^1^	X		X	
Hemoglobin measurement			X^2^		
Blood chemistry panel^10^	X^1^	X		X	
Coagulation panel^11^	X^1^			X	
Vital signs	X^1^	X	X	X	
RBC transfusion data (study or non-study)	X^1^	X		X^5^	
Concomitant medications	X^1^	X^4^		X	
Other blood components transfused		X		X	
Procedure details (as applicable, e.g., surgery)		X			
Adverse events and transfusion reactions		X	X	X^13^	
SAEs		X	X	X^13^	
Surveillance calls ^12^		X		X	
Documentation of vital status		X		X	X
Assess proportion of each RBC component transfused (e.g., 25%, 50%, 75% or 100%) For pediatric patients, the volume of the intended transfusion should be recorded			X		
Assessment of bleeding status^6^	X	X			

‡ Randomization of eligible subjects may occur any time up to 30 days prior to first study transfusion

* Day 1 of the follow-up period is the first day after the last study transfusion

^1^If results from the Screening assessments listed are available in the medical record within 30 days prior to randomization, those data may serve as the screening data and the assessments do not need to be repeated unless the subject has an RBC transfusion in the 30-day period. If an RBC transfusion occurs after determined eligibility but prior to randomization, the subject may be randomized, and those Screening assessments listed above should be repeated prior to the first study transfusion

^2^Hb measurement at 15 min to 24 h post transfusion episode (before the next RBC transfusion episode)

^3^Routine standard of care test order per local hospital SOPs

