### Sample size

The study was originally designed to enroll ~ 600 subjects to allow 95% probability that any AEs that occurs at a 1% rate would be documented in subjects that are bleeding or non-bleeding at baseline. With the later amendments to include patients undergoing chronic transfusions including RCE, the total enrollment target was increased to 600–800 enrolled subjects for the primary safety endpoints. The primary safety endpoint will be assessed in the modified intention-to-treat (mITT) population that receive at least one study RBC transfusion, a subset of the enrolled subjects. The primary efficacy endpoint will be assessed in the subset of the mITT that was non-bleeding at baseline, as active bleeding confounds the assessment of Hb increment. At least 352 non-bleeding evaluable patients (approximately 174 per treatment group) will allow for 80% power to declare non-inferiority for the primary efficacy endpoint treatment difference with a non-inferiority margin of 15% of the control mean at the two-sided 0.05 alpha level, assuming no true treatment difference and a coefficient of variance (CV) of 50%. Under the same assumptions, 468 non-bleeding evaluable subjects (234 per treatment group) will provide 90% power.

The study will also aim to enroll one-hundred-and-forty 28-day + 6-month extension subjects, including up to 30 SCD patients requiring regular repeated RCE to allow a total of three consecutive RCE procedures in at least 20 transfused evaluable patients to provide experience with repeatedly transfused subjects. Between 600 to 800 randomized subjects will be enrolled to meet the sample size targets to power the primary efficacy endpoint and the 28-day + 6-month extension period enrollment goals.

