### Statistical methods

Only patients in the mITT analysis set will be included in the efficacy analysis. Non-study RBCs received during the study transfusion period will be included to calculate the total Hb content transfused for the two efficacy endpoints in the mITT analysis set. Patients receiving non-study RBC transfusions as their first study transfusion will be excluded from the Per Protocol (PP) analysis set and only those transfusions that occur before a non-study transfusion will be analyzed. Data from the initial 28-day period and the optional 6-month extension period will be summarized together and separately.

Treatment difference in non-bleeding mITT patients will be assessed using a non-inferiority test with a pre-specified non-inferiority margin (15% of the Control mean value), stratified by site. An analysis of variance (ANOVA) model will be used to estimate and test the treatment effects while controlling for the clinical site. Non-inferiority will be declared if the lower bound of a 2-sided 95% confidence interval for the mean treatment difference (Test—0.85 × Control) is greater than or equal to zero.

For the primary efficacy endpoint, the adjusted Hb increment will be averaged over one or more transfusion episodes. An episode-specific Hb increment will be calculated by subtracting the Hb value before each transfusion episode from the Hb value taken 15-min-to-24-h after each transfusion episode. The relatively long post-transfusion assessment period is justified by prior findings that post-transfusion hemoglobin increments are not meaningfully impacted by the timing of the samples collected between 15 min and 24-h post-transfusion [14, 15]. Increments will be adjusted by the Hb content transfused in each given episode (which may contain multiple RBC components). The Hb content of each transfused RBC component will be calculated using the Hb concentration and post-sample weight of the RBC component (both measured at the blood center), and the percentage of the unit transfused (assessed at the hospital). The Hb mass of each transfusion episode is the sum of the Hb content for all RBC components transfused.

The Hb content transfused (g) for a study RBC component will be calculated as:$$post sampling weight \left(g\right)\div 1.06 \left(\frac{g}{mL}\right)\times percent of unit transfused \times hemoglobin concentration (g/mL)\div 100$$

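### The Hb-consumption non-inferiority test reuses the site-only ANOVA in about 110 mixed-diagnosis subjects and gives up precision that recorded indication and transfusion history could supply

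*Protocol article*

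**What the plan says.** Under Statistical methods, the primary endpoint is analyzed with an ANOVA used to "estimate and test the treatment effects while controlling for the clinical site". For the secondary endpoint of adjusted Hb consumption, treatment differences will be "assessed using the same non-inferiority test methods described above for the primary endpoint analysis". Non-inferiority is concluded if the upper bound of the two-sided 95% interval for Test − 1.15 × Control is at or below zero. The same paragraph adds that interactions between treatment and covariates may be explored. It names no covariate and puts no main effect into the test.

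The consumption analysis is limited to non-bleeding mITT patients who take part in both the 28-day and the 6-month periods. Table 1 lists their diagnoses as thalassemia, SCD, MDS, aplastic anemia, chemotherapy and other marrow failure. The same table records the indication for RBC transfusion at screening, together with "Medical, surgical, prior transfusion and medication history".

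**The concern.** The primary model does not carry over to consumption as well as the wording suggests. The primary endpoint is a before-after change per gram of Hb transfused, so each subject's pre-transfusion value is already subtracted. Consumption in g/kg/day has no baseline removed. It measures how much transfused Hb a subject needs over the study period. Dividing by weight and days scales for body size and follow-up, but not for diagnosis or prior need.

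Randomization is not stratified by diagnosis. Apart from what site happens to carry, differences in requirement between diagnoses therefore stay in the error term of a comparison much smaller than the primary one. What is at stake is an inconclusive result on a formal non-inferiority test, when recorded baseline data might have narrowed the interval.

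**Working it through.** **1. Inputs from the article.** Sample size sets the primary test "with a non-inferiority margin of 15% of the control mean at the two-sided 0.05 alpha level". Its planning inputs are a true difference of zero and a CV of 50%. Its stated sizes are "At least 352 non-bleeding evaluable patients (approximately 174 per treatment group) will allow for 80% power" and "468 non-bleeding evaluable subjects (234 per treatment group) will provide 90% power". Methods/design describes a "parallel group study with 1:1 allocation".

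**2. Reproducing the stated figures.** In units of the Control mean, n per arm = 2 × [0.50 × (1.960 + z) / 0.15]².
- 80% power (z = 0.842): 174.4, so 175 per arm and 350 in total, against 352 stated.
- 90% power (z = 1.282): 233.5, so 234 per arm and 468 in total, as stated.

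These figures use the variance of a plain difference. Using the variance of Test − 0.85 × Control would give about 150 and 201 per arm. No size or power is stated for consumption.

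**3. Size of the consumption comparison.** The extension target is 140, including up to 30 RCE subjects. The Randomization section counts RCE as active bleeding, so those subjects fall outside this analysis. That leaves 140 − 30 = 110, or 55 per arm, if all RCE places are filled.

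**4. Power for the stated contrast.** With no true difference,

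power = Φ{0.15 / [CV × √(1 − R²) × √((1 + 1.15²)/55)] − 1.96}.

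Here √(2.3225/55) = 0.2055. CV is taken as the spread remaining after site, and R² as the share of that remaining variance explained by the added covariates. Both are assumptions, because the article gives neither for this endpoint.

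At CV 50%:
- R² = 0: 0.15/0.1027 = 1.460, and Φ(−0.500) = 31%.
- R² = 0.25: 0.15/0.0890 = 1.686, and Φ(−0.274) = 39%.
- R² = 0.50: 0.15/0.0727 = 2.065, and Φ(0.105) = 54%.

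| Assumed CV | R² 0 | R² 0.10 | R² 0.25 | R² 0.50 |
|---|---|---|---|---|
| 30% | 68% | 73% | 80% | 93% |
| 40% | 45% | 49% | 56% | 73% |
| 50% | 31% | 34% | 39% | 54% |
| 60% | 23% | 25% | 29% | 41% |

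With the plain-difference variance (2 in place of 2.3225), the CV 50% row becomes 35%, 38%, 44% and 60%. If no RCE places were filled (70 per arm), the 1.15 contrast at CV 50% gives 38% without covariates and 64% at R² 0.50.

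**5. What 80% power would need.** The residual CV must be 0.15 / (2.802 × 0.2055) = 26%. From a CV of 50%, that requires R² = 1 − (0.2605/0.50)² = 73%.

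**The case against.** The strongest reply is that nothing here is invalid. Randomization is stratified by site, bleeding status, extension participation and RCE need. In this analysis set everyone is non-bleeding, in the extension and not on RCE, so site is the only stratification factor that still varies, and the model includes it. This stands. A reader might infer that the site-only test is biased, or that a chance imbalance of diagnoses would invalidate it. The documents do not support that: such imbalance is sampling error, which the interval already covers. The likely cost is failing to show non-inferiority, not a false claim of it.

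A reader might also infer that most between-patient variation is left in the error term. No figure in the article splits the variance. The endpoint is already scaled by weight and days. Participants says that site selection for the chronic cohort depends on investigators' access to subjects, so site may carry part of the case mix.

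Third, a usable pre-study transfusion rate is not shown to exist. Screening lists prior transfusion history without a look-back period or unit count. The 6-month look-back concerns Hb fractions in RCE patients, who are outside this analysis. This limits the fix for the rate but not for indication.

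Fourth, the power formula charges nothing for the added parameters. Six diagnosis groups cost 5 parameters, and a rate with a missing indicator costs 2. With 110 subjects, one treatment effect and an assumed 15 sites, about 110 − 1 − 1 − 14 = 94 residual degrees of freedom remain. The covariates must then explain roughly 7/94 = 7% of the residual variance to break even, so at R² 0.10 the benefit would be close to nil.

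Finally, power is claimed only for the primary endpoint, and an analysis plan not seen here may name covariates. Both points are fair. Still, the article does fix the method for this test, and exploratory interactions are not main effects in it.

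**Conclusion.** The point holds as one of precision. The formal consumption test uses treatment and site only, in a small mixed-diagnosis set, and leaves out recorded baseline information that plausibly predicts the outcome. At 55 per arm, no true difference and an assumed CV of 50%, adjustment would raise power from about 31% to about 39% (R² 0.25) or 54% (R² 0.50). If the covariates explain little, the gain is negligible. All of these figures rest on an assumed CV and R² and on a normal approximation.

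Adjustment would not by itself make this a well-powered test. At CV 50% the covariates would have to explain about 73% of the residual variance to reach 80% power. Because enrollment has closed, sample size can no longer help. The choice of model still can, since the article reports that the study remains blinded.

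**What to change.** Before unblinding, prespecify an ANCOVA for adjusted Hb consumption with treatment, site and indication category, pooling sparse categories by a rule set in advance. Add the pre-study RBC transfusion rate where the recorded history allows it to be quantified, with a missing indicator. Base the Test − 1.15 × Control interval on the adjusted means. Keep the site-only ANOVA as a sensitivity analysis, and state the CV assumed for this endpoint and the power that follows.

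The cost is a wording change in the analysis plan, some coding of recorded history and a few degrees of freedom. If the history proves not to be quantifiable, indication alone can still be used.
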